### Randomization and study drug supply

Patient drug packs will be prepared by Victoria Pharmaceuticals (Belfast, UK). Simvastatin 40 mg or identical placebo tablets will be packaged in a white opaque plastic container which will be sealed with a tamper-evident seal and labelled in compliance with applicable regulatory requirements. Each container will contain 70 tablets of the study drug for the treatment of one patient for 28 days (plus 7 days overage). All trial drugs will be packaged identically and identified only by the unique trial identifier.

Patients will be randomized in a 1:1 ratio using an automated centralized 24-hour telephone or web-based randomization service (Centre for Healthcare Randomised Trials, University of Aberdeen, UK). Randomization will be stratified by site and by vasopressor requirement (defined as any inotropic requirement except dopamine <6 mcg/kg/minute). The randomization service will allocate a unique trial identifier to each patient in accordance with the computer-generated study randomization schedule. The randomization service will confirm randomization details by email to the CTU and the study site. A confirmation email will be sent to the hospital pharmacy. The clinician will complete a trial prescription form detailing the unique trial identifier assigned to the patient. The hospital pharmacy will dispense the drug pack labelled with the corresponding unique trial identifier for the patient.

### Study drug administration

Patients will be randomized to receive once daily simvastatin 80 mg (as two 40 mg tablets) or two identical placebo tablets administered enterally via a feeding tube or orally for up to 28 days. The first dose of the study drug will be administered as soon as possible, ideally within four hours of randomization and subsequent doses will be given each morning starting on the following calendar day. If for any reason a dose is not administered at the intended time, it will be administered subsequently but not more than 12 hours after the intended time of administration.

### Post randomization withdrawals and exclusions

Patients may withdraw or be withdrawn by their representative from the trial or the trial treatment at any time without prejudice. Data recorded up to the point of withdrawal will be included in the trial analysis, unless consent to use their data has also been withdrawn. If a subject withdraws, they will be followed-up wherever possible and data collected as per protocol until the end of the trial. The only exception to this is where the subject also explicitly withdraws consent for follow-up.

### Study drug termination criteria

The study drug will be discontinued if any one of the following are met, prior to the maximum treatment period (28 days from randomization):

1. CK >10 times the upper limit of normal (ULN)

2. ALT/AST >8 times the ULN

3. Development of a clinical condition requiring immediate treatment with a statin

4. Discharge from critical care environment

5. Death

6. Discontinuation of active medical treatment

7. Patient or representative request for withdrawal of patient from the study

8. Decision by the attending clinician that the study drug should be discontinued on safety grounds

### Study drug compliance

Any omission of the study drug will be recorded in the Case Report Form (CRF) to monitor treatment compliance.

### Clinical management of patients in the trial

Patients involved in the trial will be managed according to best practice established locally on each unit. Clinicians will be encouraged to use a low tidal volume strategy of ventilation based on ideal body weight, a conservative fluid management protocol and a standardized weaning strategy. Rescue therapies such as high frequency oscillatory ventilation, nitric oxide and extracorporeal membrane oxygenation can be used according to local policy.

The exclusion criteria prevent patients with ALI who have a co-existing condition that requires treatment with a statin as part of standard clinical care being recruited. In patients where there is a clinical indication for acute and immediate treatment with a statin after randomization, for example, acute myocardial infarction, the study drug will be discontinued and a statin commenced. The patient will not be unblinded and data collection will continue. This will be recorded on the CRF. Otherwise, patients will not be commenced on a statin for the duration of the clinical trial.

### Study procedures for unblinding

As a placebo controlled, double-blind trial, patients, clinicians and research staff will be blinded to which arm of the study a patient is allocated. All trial drugs will be packaged identically and identified only by a unique trial identifier. The protocol allows for emergency unblinding in the event of significant concerns about patient safety. This option will be used if the patient’s future treatment requires knowledge of the treatment assignment. If a local investigator decides that there is justification to unblind a patient, they should make every attempt to contact the CTU, who will arrange for them to discuss unblinding with a clinical member of the trial team. Emergency unblinding will be performed by telephone contact with the randomization service. All events will be logged.

### Data collection

All data for an individual patient will be recorded in the study CRF. The majority of data will be obtained from the patient’s hospital record. Data will be collected by the site research team until hospital discharge. In the event that a patient is transferred to another hospital, the site research team will liaise with the receiving hospital to ensure complete data collection. The EQ-5D will be administered face-to-face at discharge. The EQ-5D and resource use questionnaires will then be administered by post or by telephone after the patient has been discharged from hospital. On discharge the participating site will provide the trial manager at the CTU with the name, address and contact details for the patient. Postal health-related quality of life and resource utilization questionnaires will be sent out and collected by the CTU. If questionnaires are not returned telephone contact will be made to the trial patient to check that the questionnaire has been received and the patient is happy to complete it, followed by a second copy of the questionnaire. If the second questionnaire is not returned the patient will be contacted by telephone and the outcome data collected over the telephone. Trial patients will be asked to let the CTU know if they move house at any time after hospital discharge.

Patient identification on the CRF and questionnaires will be through their unique trial identifier allocated at the time of randomization and patient initials.

### Monitoring and reporting adverse events

HARP-2 is recruiting a population that is already in a life-threatening situation; it is expected that many of the participants will experience adverse events (AEs). Events that are expected in this population (that is, events that are in keeping with the patient’s underlying medical condition) should not be reported as AEs. If any AEs are related to the study drug (that is, are adverse reactions) they must be reported on the AE form within the CRF.

SAEs thought to be related to the study drug or SUSARs (that is, their nature or severity is not consistent with the summary of product characteristics for simvastatin) will be reported to the CTU within 24 hours of becoming aware of their occurrence. The CTU will inform the sponsor and regulatory authorities within the required timelines as per the regulatory requirements.

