### Safety

The frequency with which the following events occur will be reported: (1) creatine kinase (CK) >10 times the upper limit of normal; (2) alanine transaminase (ALT)/aspartate aminotransferase (AST) >8 times the upper limit of normal; (3) need for renal replacement therapy in patients with CK elevated >10 fold; and (4) serious adverse events (SAEs) and occurrence of suspected unexpected serious adverse reactions (SUSARs). Safety monitoring (CK and liver transaminases) is undertaken at days 3, 7, 14, 21 and 28.

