### Trial oversight

The Chief Investigators will have overall responsibility for the conduct of the study. The Trial Management Group will have responsibility for the day to day operational management of the trial. Trial oversight will be provided by a Trial Steering Committee (TSC) comprising investigators, clinicians and trialists. The TSC will operate within the relevant CTU Standard Operating Procedure (SOP). An independent Data Monitoring and Ethics Committee (DMEC) will monitor the safety of participants enrolled in the trial through regular review of adverse event reports. The reports provided to the DMEC will include information on the AEs reported, deaths from all causes at 28 days and recruitment, along with any other data that the committee may request. The DMEC will advise the TSC if, in their view, the randomized comparisons have provided both (i) 'proof beyond reasonable doubt' that for all, or some, the treatment is clearly indicated or clearly contra-indicated and (ii) evidence that might reasonably be expected to materially influence future patient management. Following a report from the DMEC, the TSC will decide what actions, if any, are required. Unless the DMEC requests cessation of the trial the TSC and the collaborators will not be informed of the reports provided to the DMEC.

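### The safety outcome promises SAE frequency without limit, but the reporting rule gives a route only for events judged drug-related, so the figure could be misread as all-cause

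*Protocol article*

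**What the plan says.** Three sections of the protocol article bear on this.

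- **Safety.** The section opens with "The frequency with which the following events occur will be reported" and gives four items. The fourth is "serious adverse events (SAEs) and occurrence of suspected unexpected serious adverse reactions (SUSARs"). No restriction to related events is attached to the SAEs. The other three items are CK above 10 times the upper limit of normal, ALT/AST above 8 times that limit, and renal replacement therapy, the last only in patients whose CK is raised more than 10-fold.
- **Monitoring and reporting adverse events.** "Events that are expected in this population", explained as those that fit the patient's underlying condition, "should not be reported as AEs". No exception is made for serious events. For adverse events related to the study drug, "they must be reported on the AE form within the CRF". For serious events the rule covers "SAEs thought to be related to the study drug or SUSARs", and these "will be reported to the CTU within 24 hours of becoming aware of their occurrence".
- **Trial oversight.** The DMEC's safety monitoring rests on the adverse event reports that it examines at intervals during the trial. On their content the section says: "The reports provided to the DMEC will include information on the AEs reported, deaths from all causes at 28 days and recruitment", and the same sentence lets the committee request any other data.

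**The concern.** The outcome and the collection rule do not describe the same quantity. A reader of the final report who sees a line headed SAEs will take it as all serious events by arm. Under the rule as written it would be a tally of individual causality opinions, formed by staff blinded to treatment in patients who already have life-threatening organ failure.

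This matters because an event can both fit the disease and be caused by the drug. No one can reliably separate the two at the bedside in a single patient. Randomization makes the separation unnecessary, since a drug effect appears as a difference between arms, but only when events are counted whatever their presumed cause. A low and balanced count of related SAEs is weak evidence of safety. Labelled simply as SAEs, it would look stronger than it is.

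The same filtered stream is the first item in the DMEC's default report, so the question also touches monitoring during the trial.

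**Working it through.** The article states no figure for this point, so there is nothing to reproduce. The check sets the rule against the outcome.

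**Step 1. Where each kind of serious event goes under the reporting rule**

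| Site's judgement of a serious event | Stated route | In an unrestricted SAE frequency? |
|---|---|---|
| Related to study drug | AE form, and CTU within 24 hours | Yes |
| Not related, in keeping with the underlying condition | Sites told not to report it as an AE | Yes |
| Not related, not in keeping with the condition | Not barred, but no route stated | Yes |

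The outcome in the Safety section covers all three rows. The reporting section gives a route for the first only. SUSARs are suspected reactions, so they fall within the first row and do not widen it.

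**Step 2. How far apart the two quantities can be**

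Inputs: 540 patients (Power and sample size estimate) and mortality of about 30% to 40% in ALI (Background). Assumptions: a death counts as a serious event (the article does not define SAE), and the background mortality applies to the trial population.

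- 0.30 × 540 = 162
- 0.40 × 540 = 216

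An unrestricted SAE frequency would therefore include some 162 to 216 fatal events, plus all non-fatal serious ones. Under the rule, only the deaths judged related would enter the SAE count. This measures the gap between label and content. It does not measure missed harm, because deaths are reported as an outcome in their own right. For non-fatal SAEs, the article gives neither a rate nor a proportion judged related, so no count can be derived.

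**Step 3. What is compared by arm without any attribution**

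- *Outcome measures:* mortality at 28 days, at critical care discharge, at hospital discharge and at 12 months; change in SOFA to days 3, 7, 14 and 28; non-pulmonary organ failure free days, built from cardiovascular, renal, liver and neurological support.
- *Safety:* the CK and ALT/AST thresholds, measured at days 3, 7, 14, 21 and 28.
- *Statistical analysis plan:* analysis is by intention to treat.

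Two limits remain. Organ failure free days pools four organ systems, so an excess in one can be diluted. Renal replacement is a listed safety event only after a CK rise of more than 10-fold, so renal failure without that rise is not on the safety list, though renal support does enter the pooled outcome.

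**Step 4. What the DMEC sees by default**

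Its stated content is reported AEs (filtered as in Step 1), all-cause deaths at 28 days, and recruitment. Organ support and the CK and transaminase results are not named. They are available if the committee asks. No interim efficacy analysis is planned, so the article schedules no other interim look at organ support.

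**The case against.** The strongest reply is that the trial already compares serious deterioration by arm and that the mismatch is only one of wording. Much of that is right, and it rules out three stronger readings that a reader might draw.

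- *Drug-caused organ deterioration would go uncounted.* Not supported. Organ support, SOFA and mortality are outcomes whatever the cause, and so are the CK and transaminase thresholds. A substantial excess of organ failure on simvastatin would bear on these outcomes.
- *Neither the final report nor the DMEC sees serious events by arm.* Not supported. Related SAEs and SUSARs are captured, all-cause 28-day deaths go to the DMEC by default, and the committee can request anything else. The Trial oversight section asks it to judge the randomized comparisons, which implies review by arm.
- *Only drug-related events can be recorded.* This goes slightly too far. The exclusion covers events that fit the illness; unexpected events of unclear cause are not barred, and the 24-hour sentence concerns expedited reporting rather than everything on the CRF.

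Two further arguments deserve weight. Restricted adverse event reporting is an understandable choice in critical illness, and the article gives that reason. And this is a condensed article: the full protocol may state how other SAEs are recorded.

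What survives is narrower. The restriction itself can stand, but the outcome should then be named for what is collected. A silence could be left to the full protocol; here two statements in the same article disagree, and a reader cannot tell which one governs the reported figure. The right to request data also makes routine review of organ support depend on the committee thinking to ask.

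**Conclusion.** The point holds in limited form. The article promises an unrestricted SAE frequency while its reporting rule would deliver essentially the SAEs judged drug-related, and the default DMEC report adds only 28-day deaths and recruitment to that filtered stream.

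The consequence is a safety line that could be misread as all-cause, together with a default monitoring report thinner than the data already collected would allow. It is not a loss of the all-cause comparison in the final analysis. The primary outcome, the sample size and the efficacy analyses are unaffected. The change is worth making because it costs little and settles what a headline safety figure means.

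The conclusion assumes that sites follow the reporting rule as worded and that the full protocol adds no separate route for unrelated or disease-related SAEs. If it does, only the article's wording and the DMEC table need attention.

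**What to change.** 1. **Reconcile the two sections.** Either rename the fourth safety item *SAEs judged related to study drug, and SUSARs*, or keep the present label and state how all SAEs, including those that fit the underlying illness, are recorded.
2. **Add one attribution-free table by arm** to the default DMEC report and to the final safety section, with all randomized patients as denominator: all-cause deaths; renal, liver and cardiovascular support, each shown separately; and CK and ALT/AST results. Show support beside deaths, since a patient who dies early accrues few days of support. Renal support would then be visible whether or not CK rose.
3. **Include study drug stopped on safety grounds** if the CRF records the reason. The article lists this as a termination criterion but does not say that the reason is captured, so this should be checked first.

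The cost is one label and one table drawn mainly from data already collected, with no added reporting burden under the relabelling option. The alternative of recording all SAEs would add site work. The downside of the table is one more set of comparisons to interpret; it should be read descriptively, without formal testing.

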### End of trial

The trial will end when 540 patients have been recruited. The trial will be stopped prematurely if: mandated by the Research Ethics Committee, the Medicines and Healthcare products Regulatory Agency (MHRA), the Irish Medicines Board (IMB), the Sponsor (for example, following recommendations from the Data Monitoring and Ethics Committee (DMEC) or funding for the trial ceases.

### Statistical analysis plan

Standard approaches will be used to detect patterns in missing data. Analyses will be on an intention-to-treat basis. As VFDs are unlikely to be normally distributed, the groups will be analyzed by comparing the medians and 95% confidence intervals (CI). The comparison of other continuous outcomes will be by analysis of variance, including covariates where appropriate. Statistical diagnostic methods will be used to check for violations of the assumptions, and transformations will be performed where required. A statistical interaction test will be used to assess differences in treatment effects between the subgroups. For binary outcome measures risk ratios and associated 95% CI will be calculated. Binary variables assessed daily will be analyzed using logistic regression analysis corrected for days at risk. Time-to-event outcomes will be analyzed by survival methods and reported as hazard ratios with 95% CI. An interim analysis of efficacy is not planned.

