### Power and sample size estimate

The mean (standard deviation; SD) VFDs in 432 patients with ALI was 12.7 (10.6) days [16]. The SD (10.6) for VFDs in ALI used for the sample size calculations is similar to the SD for VFDs that has been consistently reported in other large multi-center clinical trials [17-19]. There are no prospective trials in patients with ALI to predict the treatment effect size of simvastatin to improve VFDs. In a recent retrospective study, statin usage in patients with ALI was associated with a 31% increase in VFDs [20]. Our observational data showed a 37% relative improvement in mortality in patients who received a statin [4]. In our proof of concept study, OI and SOFA scores improved by 50% to 66%, respectively, in the simvastatin-treated group [11]. Pre-treatment with simvastatin decreased a range of pulmonary inflammatory mediators induced by LPS in healthy volunteers by between 34% to 65% [10]. On the basis of these data, a conservative treatment effect of 20% has been estimated for this study.

A sample size of 524 subjects (262 in each group) will have 80% power at a two-tailed significance level of 0.05 to detect a 20% difference in VFDs. To estimate loss after recruitment, previous data from the PAC-Man trial were used where 2.4% of recruited patients or their relatives subsequently withdrew their consent, or were randomized in error [21]. Thus, estimating a dropout rate of 3% the study will require a total of 540 patients with 270 in each group (Figure 1).

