### Subgroup analyses

Four subgroup analyses are planned to analyze whether treatment effect is modified by age, vasopressor requirement (defined as any inotropic requirement except dopamine <6mcg/kg/minute); etiology of ALI (due to sepsis versus non-sepsis) and CRP level at baseline. Subgroup analyses will use a statistical test for interaction and will be reported using 99% CI. The trial statistician has written a detailed statistical analysis plan (SAP).

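### The sample size is for a difference in mean ventilator-free days, but the stated primary analysis compares medians, so the stated 80% power does not belong to the stated analysis

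*Protocol article*

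**What the plan says.** *Power and sample size estimate* starts from a mean and SD: "The mean (standard deviation; SD) VFDs in 432 patients with ALI was 12.7 (10.6) days". It then adopts an effect: "a conservative treatment effect of 20% has been estimated for this study". The result is: "A sample size of 524 subjects (262 in each group) will have 80% power at a two-tailed significance level of 0.05". A 3% allowance for dropout brings the total to 540.

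*Statistical analysis plan* fixes the comparison for the primary outcome: "As VFDs are unlikely to be normally distributed, the groups will be analyzed by comparing the medians and 95% confidence intervals (CI". Other continuous outcomes go to analysis of variance.

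*Outcome measures* gives a score of zero to patients who die within the 28 days or are still ventilated at the end of them. The article gives no control median, no target difference in medians, no share of zeros, and no adjustment of the sample size for a median or rank method.

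**The concern.** The sample size and the primary analysis address different quantities. A 20% rise in the mean does not fix how far the median moves, and the sampling error of a median depends on how many patients lie close to it. With a mass at zero and another at high values, the median can fall where patients are sparse and be poorly estimated.

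The reason given for the switch is weak. Non-normal individual values do not invalidate a comparison of means with 262 per group on a scale bounded at 0 and 28.

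At stake is a false negative on the primary outcome. The article supports its effect size partly with a 37% relative improvement in mortality. Fewer deaths mean fewer zeros, and that is the route on which a median comparison performs worst.

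**Working it through.** **Inputs from the protocol article.** Mean 12.7, SD 10.6, effect 20%, 262 per group, two-sided 0.05, 80% power, dropout 3% (*Power and sample size estimate*). Zero scoring comes from *Outcome measures*. Mortality of about 30–40% (*Background*) is a rough guide to the zeros.

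**1. Reproducing the sample size.** The difference is 0.20 × 12.7 = 2.54 days.

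- n per group = 2 × (1.960 + 0.842)² × 10.6² / 2.54² ≈ 273.4, so 274 (548 in total).
- Power at 262: SE = 10.6 × √(2/262) = 0.926; 2.54/0.926 − 1.960 = 0.783; power = 78.3%.
- With the difference rounded to 2.6 days (20% of 13, a rounding that the article does not state), the t-test calculation gives exactly 262 per group.
- Dropout: 524/0.97 = 540.2, in line with 540.

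The 524 is thus a two-sample comparison of means with a lightly rounded effect. The gap between 548 and 524 costs under 2 points of power and is not the issue. A usual rank-test inflation (274/0.864) would have given about 317 per group, so none was applied.

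**2. How many zeros the stated figures allow.** E[X²] = 12.7² + 10.6² = 161.29 + 112.36 = 273.65. By the Cauchy–Schwarz inequality, P(X>0) ≥ 161.29/273.65 = 0.589, so at most about 41% can be zeros. At 40% zeros, the non-zero patients would have mean 12.7/0.6 = 21.17 and variance 273.65/0.6 − 21.17² ≈ 8, an SD of only about 2.8 days. At 35% the same arithmetic gives an SD of about 6.3 days. So 40% is close to the limit. I use 25–40%, as an assumption.

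**3. Simulation.** VFDs are a zero spike plus a beta-binomial part, calibrated to mean 12.7 and SD 10.6, with 262 per group and 800 trials per case. The true mean rises to 1.2 × 12.7 = 15.24. The median comparison uses a bootstrap 95% CI for the difference in medians. Cells show power in %, median comparison / t-test on means. The SE ratio is median difference over mean difference, under no effect.

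| Zeros | SE ratio | Proportional odds | Fewer zeros only | Non-zero patients only |
|---|---|---|---|---|
| 25% | 2.4 | 62 / 80 | 48 / 82 | 77 / 78 |
| 30% | 2.3 | 57 / 77 | 47 / 82 | 84 / 75 |
| 35% | 2.1 | 61 / 81 | 45 / 82 | 92 / 73 |
| 40% | 1.5 | 45 / 79 | 26 / 80 | 91 / 74 |

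With the effect present, the SE ratio is 1.7–2.4 for 25–35% zeros and 0.9–1.1 at 40%. Monte Carlo error is about 1–2 points per power figure.

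**4. Checks.**

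- A separate simulation on the same calibration gave the median comparison 44–62% (proportional odds), 27–47% (fewer zeros) and 62–86% (non-zero patients only).
- An effect split equally between fewer zeros and more days among non-zero patients gave 56–65% for 25–36% zeros, against 76–82% for means, but 90% at 40% zeros.
- Under no effect, the t-test rejected in 3.9–5.9% of trials, so non-normality does not upset its 5% level. The bootstrap median interval rejected in 1.5–3.4%, so a little of its shortfall is conservatism. For 25–35% zeros, a test using the bootstrap SE instead gave 62–67% (proportional odds) and 46–54% (fewer zeros), still well short of 80%.

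**The case against.** **Power is not always lost.** A larger SE alone does not settle power, because a 20% rise in the mean can move the median by more than 2.54 days (3.2–6.3 days in these simulations at 25–35% zeros). If the drug only speeds weaning among patients who do wean, the median comparison has 62–92% power, depending on how the added days are spread, and it can beat the mean. This stands. A reader might infer that the plan cannot deliver its stated power; the documents do not say by which route the effect would act and do not support that.

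**The share of zeros is assumed.** This also stands. The roughly twofold loss of precision holds for 25–35% zeros and fades at 40%. The power shortfall under the first two effects does not fade: at 40% it is larger.

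**The sentence may be shorthand for a rank test with medians reported.** The article names no test or interval method, and a detailed SAP exists. A Mann–Whitney test has 73–91% power for 25–35% zeros and 68–100% at 40%, so it keeps roughly the stated power in most settings. But the article says medians, and a rank test is not in general a test of medians, so the wording would still need correcting.

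**Two further readings go beyond the text.** One is that the arms will be judged by whether their separate intervals overlap, so that there is no 5% test. The article fixes a two-tailed 0.05 level in its sample-size section and nowhere describes such a rule. The other is that the subgroup interactions will be tested on medians. The article says only: "Subgroup analyses will use a statistical test for interaction and will be reported using 99% CI". It does not give the scale.

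**Conclusion.** The concern holds as a mismatch between the sample size and the primary analysis. The stated 80% is the power to detect a 20% difference in means, and no power is shown for the comparison of medians that the article states.

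Read literally, that comparison has about 44–62% power under a proportional-odds effect and about 26–48% if the effect is fewer zeros, against about 73–83% for means. It reaches about 80% or more in some cases where the effect is confined to non-zero patients, and for an equally split effect at the 40% limit. These figures rest on an assumed 25–40% zeros, an assumed shape for the non-zero days, a true mean gain of 2.54 days and a bootstrap interval for the median difference. The mismatch itself rests on none of them.

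**What to change.** In *Statistical analysis plan*, before unblinding, replace the comparison of medians. Make the primary analysis the difference in mean VFDs between groups, with a 95% CI and a two-sided 5% test, using a robust or bootstrap standard error. This matches the sample-size section. Keep a Wilcoxon or proportional-odds analysis as sensitivity, and report medians and interquartile ranges descriptively. Bring the SAP into line.

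No extra patients or data are needed. There are two costs. The mean of a two-humped outcome describes a typical patient less well, which is why the medians stay as description. The change of primary analysis must also be dated and justified, because 293 of the 540 patients were enrolled by December 2012. The trial is double-blind and plans no interim efficacy analysis, so the change can still be made without knowledge of the results. If the sponsor prefers to keep medians, the sample size needs its own justification on that scale.
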